## Non-permitted medications

The following therapies are not permitted during TILT:

- Any chemotherapy or immunotherapy (participants who receive the intervention only)
- Granulocyte colony stimulating factor (GCSF) or Granulocyte macrophage colony-stimulating factor
- Other known immunosuppressive or immunomodulatory medication

## Permitted interventions

Interventions to control pleural fluid and procedures to control pain (e.g. cordotomy) can be employed as necessary, but ideally should be avoided within 14 days of OK432/BCG delivery. Thoracoscopy to the ipsilateral pleural space should be avoided in the 14 days after OK432/BCG delivery. Insertion of in-dwelling medical devices, e.g. Hickman or PICC lines, portacaths, IPCs, should be avoided within 14 days of OK432/BCG delivery but can be undertaken outside this period. Participants who have a medical device in situ at the start of the trial can participate in the trial without limitation.

## Non-permitted interventions

Thoracic surgery to the ipsilateral pleural space or chest wall should be avoided unless absolutely necessary for life-saving reasons. Where thoracic surgery is undertaken, prophylactic antibiotics should be considered to prevent post-operative complications.

## Data on concomitant medications and interventions

All concomitant medication taken during the trial will be recorded on eCRFs including all prescription, over-the-counter (OTC), herbal supplements, and IV medications and fluids. Documentation of concomitant medication should include generic name, dose, frequency, route, date of any changes occurring during the trial period, and indication. All interventions undertaken during the trial period will be recorded on eCRFs.

# TRIAL FOLLOW UP ASSESSMENTS

## Trial visits

As well as an initial screening visit at Week 0, participants will attend 3 trial assessment visits within the subsequent 12 weeks, with participants in the intervention arm returning for two additional visits; one to receive OK432/BCG within 14 days of randomisation (i.e. days 0-14) and a follow-up safety visit on day 3 post-IMP administration. Trial visits will take place at 3 weeks, 6 weeks and 12 weeks post-randomisation.

Participants who receive an IMP will also be contacted by telephone by a member of the trial team, daily for up to 5 days after IMP administration, to check on their well-being. Trial visits must occur as scheduled +/- 3 days, with the exception of the 3 day post intervention visit which must occur on day 3. Trial procedures and assessments for each visit are detailed in section 9.7. The trial flowchart is shown in section 2.4.

Having completed the 12 week trial period, participants will return to clinical follow up as part of the ASSESS-meso. They will participate in ongoing data collection in accordance with the ASSESS-meso protocol which will continue until death, loss to follow up or withdrawal from ASSESS-meso.

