This project will investigate intra-pleural bacterial immunotherapy in MPM using an innovative trial design, the Trial within a Cohort (TwiC)^41^. Participants will be recruited from an existing observational cohort, consisting of regular clinical and radiological monitoring (the ASSESS-meso study). From ASSESS-meso, 8 eligible participants will be randomly selected for either the OK432 or BCG arm of the trial. OK432 or BCG will be delivered intra-pleurally as a single dose via an indwelling catheter. Outcome data will be compared with control participants from ASSESS-meso. Qualitative interview will be undertaken to assess acceptability of the methodology to participants.

*Aims*

The aims of this research are:

- To assess the feasibility and acceptability of the TwiC methodology
- To explore the role of intra-pleural bacterial immunotherapy in people with MPM
- To answer the question “Is it feasible to undertake a three-armed TwiC of intra-pleural immunotherapy in MPM and is it acceptable to participants and relatives?”

If feasibility is demonstrated, results will inform the design of a full-scale TwiC of intra-pleural bacterial immunotherapy using one or both agents from this study, depending on results.

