**Follow up 1**

3 days post intervention (or week 3 for controls)

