## End of trial (EoT)

Trial recruitment will cease in November 2019, regardless of the number of participants enrolled. EoT date, therefore, will be 12 weeks after enrolment of the 12^th^ trial patient or 12 weeks after the recruitment window closes, whichever happens first. At EoT, participants will return to clinical follow up within ASSESS-meso, which will continue until death, loss to follow up or withdrawal from the study. Data from ASSESS-meso will be used to evaluate overall survival at EoT.

|  |  | **Screening**  **Week 0*** | **Intervention**  **Day 0-14** | **3 days post-intervention**  **(Week 3)** | **Week 6** | **Week 12** |
| --- | --- | --- | --- | --- | --- | --- |
| **Clinical assessment** | Assessment of eligibility | X | **X** |  |  |  |
|  | History of pleural interventions | X |  | X | X | X |
|  | Previous oncological treatment | X |  |  |  |  |
|  | Medication history | X | **X** | X | X | X |
|  | WHO/ECOG performance status | X | **X** | X |  |  |
|  | Vital signs, pulse oximetry | X | **X** |  |  |  |
|  | Physical examination | X |  |  |  |  |
|  | Insertion of IPC (if not already in situ) | X |  |  |  |  |
|  | Pleural fluid drainage diary review | X |  | X | X | X |
|  | Documentation of AEs |  | **X** |  | X | X |
| **Blood tests** | Screening blood tests (HIV screen, hepatitis screen, immunoglobulins, random glucose, thyroid function tests) | X |  |  |  |  |
|  | Pregnancy test  (if female <55 yrs) | X |  |  |  |  |
|  | Coagulation panel | X |  |  |  |  |
|  | Trial blood tests (Full blood count, urea & electrolytes, liver function tests, C reactive protein) | X | **X** | X | X | X |
|  | Serum mesothelin | X |  | X | X | X |
|  | Pleural fluid sampling and storage | X | **X** | X | X | X |
|  | Mantoux test (if logistically possible, BCG arm only) | X |  |  |  | X |
| **Randomisation & intervention** | Random selection | X |  |  |  |  |
|  | Informed consent for TILT |  | **X** |  |  |  |
|  | Administration of OK432/BCG |  | **X** |  |  |  |
| **PROMS** | Breathlessness & chest pain VAS score | X |  | X | X | X |
|  | Daily VAS score completion |  |  |  |  |  |
|  | EQ-5D-5L QoL questionnaire | X |  | X | X | X |
| **Radiological imaging** | Chest x-ray | X | **X** | X | X | X |
|  | Thoracic ultrasound | X | **X** | X | X | X |
|  | CT chest (within preceding 2 weeks) | X |  |  |  | X |
| **Qualitative research** | Participant interviews |  |  |  |  | X |
|  | Focus groups with relatives/carers |  |  |  |  | X |

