# ADVERSE EVENT MONITORING

## Definitions

*Adverse Event (AE)*

Adverse Events (AEs) are any untoward medical occurrence in a patient or clinical trial subject administered an investigational medicinal product (IMP), medical device or intervention and which does not necessarily have a causal relationship with this treatment. This includes any unfavourable and unintended signs, including abnormal laboratory results, symptoms or a disease temporarily associated with an investigational product.

AE must always be recorded on an eCRF and in the patient's medical notes.

*Adverse Reaction (AR)*

Adverse Reactions (ARs) are adverse events where there is evidence to suggest there is a causal relationship between the event and the IMP.

*Serious Adverse Event (SAE) or Serious Adverse Reaction (SAR)*

Serious Adverse Events (SAEs) are defined as any untoward medical occurrence(s) that results in:

- death
- real and immediate threat to life
- hospitalisation
- prolongation of existing hospitalisation
- persistent or significant disability or incapacity
- a congenital anomaly or birth defect
- other health event which in the opinion of the clinician is serious

*Serious Adverse Reaction (SAR)*

Any SAE that is classed as serious in nature and which is consistent with the information about the IMP set out in the summary of product characteristics (SmPC) for that product or listed as an expected reaction in the trial protocol.

*Suspected Unexpected Serious Adverse Reaction (SUSAR)*

Any SAE/SAR that is suspected to be caused by the IMP, but which is not consistent with the information available about the IMP set out in the SmPC for that product or listed as an expected reaction in the trial protocol. If the event is not listed as expected, or has occurred in a more serious form than anticipated, it should be considered a SUSAR.

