## Analysis plan

Basic descriptors will be used to summarise the characteristics of the overall trial population, each arm, and participants who decline any element of the trial. The characteristics of people who decline participation will be compared with the trial population using means, confidence intervals, chi-squared and unpaired T-tests. If possible, multivariable regression modelling will be undertaken to explore which factors were associated with non-acceptance of OK432/BCG.

Feasibility outcomes, including recruitment, randomisation and trial completion rates, will be described for the overall trial and for each arm. Secondary outcomes will be summarised for each arm based on randomisation, i.e. intention to treat. Per protocol and compliance averaged causal effects (CACE) analysis will be undertaken as secondary analyses for clinical efficacy outcomes.

Time to event data will be analysed using the Kaplan-Meier method. Cox proportional hazards modelling will be used to calculate hazard ratios for death and pleurodesis. Univariable modelling will be used, followed by multi-variable methods to control for potential confounders. The time-independent confounders to be considered are age, sex, performance status, tumour histology and whether chemotherapy was received. Time-dependent confounders that will be adjusted for are the time between diagnosis with MPM and baseline assessment, and length of time the IPC was in situ. The main analysis will include all patients. A priori sub-group analyses will stratify patients according to time since diagnosis (≥8 weeks versus <8 weeks) and whether chemotherapy was received.

Pleurodesis rates will be calculated for the whole population, and in the sub-group of patients who’s IPC had been in situ for less than 6 weeks at baseline assessment.

Outcomes with repeat measurements, e.g. PROMS and biomarker responses, will be analysed using regression modelling with adjustment for baseline values. Survival rates will be compared with national survival data, and survival rates from previous clinical trials of new treatments in MPM. Progression-free survival rates will be compared to validated values for acceptable clinical activity of new oncological agents in MPM.^99^

Statistical analysis will be undertaken using Stata (StataCorp LP) version 14, with support from YTU.

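### Controls lack the dosing visit and post-dose calls given to treated participants, so by-arm adverse-event counts are expected to show more mild, laboratory and imaging events in the treated arms even with no drug effect

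*Protocol*

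**What the plan says.** **Contacts.** Section 9.1 states that after screening "participants will attend 3 trial assessment visits within the subsequent 12 weeks" (Weeks 3, 6 and 12), "with participants in the intervention arm returning for two additional visits": one for dosing and one for safety on day 3. Recipients are also telephoned "daily for up to 5 days after IMP administration, to check on their well-being". No equivalent is given for controls.

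The trial flowchart differs. It has a single Follow up 1, placed at "3 days post intervention (or week 3 for controls". The schedule table (9.7) likewise has one column for day 3 and Week 3, with the same bloods, chest x-ray and ultrasound ticked for both groups. Section 6.5 says that controls' visits match the TILT schedule.

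**What counts and when it is collected.** The definition in 12.1 is broad: "This includes any unfavourable and unintended signs, including abnormal laboratory results, symptoms or a disease temporarily associated with an investigational product". Section 12.4 has adverse events collected at every visit for all participants, and 9.4 has them assessed at each assessment visit. The schedule row, however, reads "Documentation of AEs | | X | | X | X", which leaves the day-3/Week-3 cell blank.

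**How the data are used.** Section 2.3 lists adverse events as a secondary outcome; the list in 13.2 omits them. Section 13.3 says: "Secondary outcomes will be summarised for each arm based on randomisation, i.e. intention to treat". The abstract says: "Outcome data will be compared with control participants from ASSESS-meso". No passage separates events by the contact at which they were found.

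**The concern.** The number of adverse events recorded depends on how often someone looks. Treated participants are examined, tested and telephoned in the days around dosing, while controls are first seen at Week 3. Section 9.1 does not schedule formal adverse-event questioning on the calls, but 12.5 requires every adverse event to be recorded, so anything mentioned on a call enters the data.

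In advanced mesothelioma, fever, pain and abnormal bloods can occur without any trial drug. A short-lived event of that kind is more likely to be recorded in a treated participant than in a control. At stake is the treated-versus-control reading of tolerability that will inform the full-scale trial: part of an apparent excess could reflect surveillance and not toxicity.

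**Working it through.** The protocol gives no adverse-event rate and no calculation to reproduce; the sample of 12 (8 selected for OK432 or BCG, 4 controls) rests on previous feasibility studies.

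**Step 1. Count contacts after screening, to Week 12.**

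| Source | Treated | Control | Ratio |
|---|---|---|---|
| 9.1, visits only | dosing + day 3 + Weeks 3, 6, 12 = 5 | 3 | 1.67 |
| 9.1, with up to 5 calls | 10 | 3 | 3.33 |
| Flowchart/schedule, visits only | dosing + day 3 + Weeks 6, 12 = 4 | 3 | 1.33 |
| Flowchart/schedule, with up to 5 calls | 9 | 3 | 3.00 |
| Adverse-event ticks in the schedule | dosing + Weeks 6, 12 = 3 | 2 | 1.50 |

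The calls are counted at their maximum.

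**Step 2. Chance of at least one abnormal laboratory or imaging finding with no drug effect.** Bloods and imaging are done at visits, not on calls, so panels equal visits. The yield per panel, p, is an assumption: 10%, 20% or 30%, equal and independent across panels. The chance over k panels is 1 − (1 − p)^k.

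| p | 3 panels (control) | 4 panels (schedule) | Excess | 5 panels (9.1) | Excess |
|---|---|---|---|---|---|
| 10% | 1 − 0.9³ = 27.1% | 1 − 0.9⁴ = 34.4% | 7.3 points | 1 − 0.9⁵ = 41.0% | 13.9 points |
| 20% | 1 − 0.8³ = 48.8% | 1 − 0.8⁴ = 59.0% | 10.2 points | 1 − 0.8⁵ = 67.2% | 18.4 points |
| 30% | 1 − 0.7³ = 65.7% | 1 − 0.7⁴ = 76.0% | 10.3 points | 1 − 0.7⁵ = 83.2% | 17.5 points |

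**Step 3. Relax independence.** If an abnormality, once present, appears on every panel, the chance is p in both groups and the excess is zero. Real data lie in between.

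**Step 4. Scale to the trial.** With 4 per arm, 7-10 points is about 0.3-0.4 of a participant (4 × 0.073 to 4 × 0.103), and 14-18 points is about 0.6-0.7 (4 × 0.139 to 4 × 0.184).

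**Step 5. Intention to treat.** Participants who decline get neither dosing visit nor calls. At an assumed 75% acceptance, the contact ratio of 3.33 falls to (0.75 × 10 + 0.25 × 3)/3 = 2.75, and 1.33 falls to (0.75 × 4 + 0.25 × 3)/3 = 1.25.

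**Step 6. Timing under the merged visit.** Dosing is on days 0-14, so day 3 after dosing falls on days 3-17 after randomisation; the control visit falls at day 21. The shared visit then covers different stretches of follow-up in the two groups.

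**The case against.** - **No adverse-event comparison is fixed.** Section 13.3 speaks of summaries, 13.2 omits adverse events, and the comparison with controls comes from a general sentence in the abstract. A statistical analysis plan could set the tabulation. This stands in part: no test is named. But side-by-side summaries invite the comparison, and if the detecting contact is not captured prospectively, no later plan can reliably recover it.
- **The schedule merges day 3 with Week 3.** This stands. A reader might take 14-18 points as the size of the problem, but that holds only under section 9.1; the schedule supports 7-10.
- **Other sources narrow the gap.** Causality grading (12.3) means that toxicity is not read from raw excess alone. Section 9.3 plans daily breathlessness, chest pain and quality-of-life reports for a period between Weeks 0 and 3 in all participants, although no cell is ticked in the schedule's daily-score row. Part of the dosing-visit assessment, including the x-ray for trapped lung, precedes instillation (7.3). All of this stands, but none of it supplies a laboratory or imaging finding that was never looked for in controls.
- **The agents are treated alike.** A reader might infer that the choice between OK432 and BCG is biased. The documents do not support that: both arms have the same dosing visit, day-3 visit and calls, and the only scheduled arm-specific test is an optional Mantoux test.
- **Chance and recall.** A reader might also infer that the treated arms will show more events. That is too strong. Full recall of symptoms at shared visits would bring the ratio to 1.0, and with about 4 per arm chance may dominate.

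**Conclusion.** The point holds as an expected distortion of limited and uncertain size. Unequal ascertainment is built into the contact schedule, and nothing in the protocol keeps it out of the treated-versus-control adverse-event figures. The dosing visit and calls are treated-only under every reading; whether the day-3 visit is extra depends on which passage is followed.

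The estimated false excess rests on an assumed 10-30% yield per panel, independence between panels and full acceptance of treatment. Persistence of abnormalities and refusals both reduce it. It concerns mild symptoms and laboratory and imaging findings; deaths and serious events are much less sensitive to contact frequency. The additional safety contacts are not themselves an error. The weakness is the unqualified by-arm use of what they find.

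**What to change.** 1. Reconcile section 9.1 with the flowchart and schedule on whether the day-3 visit replaces Week 3 or is additional. If the merged visit stays, state that its timing differs between the groups.
2. Reconcile the blank adverse-event cell at day 3/Week 3 in the schedule with 9.4 and 12.4.
3. Add a field to the adverse-event form for the contact at which each event was found.
4. In 13.3, base the treated-versus-control comparison on deaths, serious adverse events, and adverse events and laboratory or imaging findings elicited in the same way at visits that both groups attend. At each such visit, ask every participant about the whole interval since the last shared visit, whatever was recorded in between. Without this, dropping treated events found at extra contacts while controls recall the same period at Week 3 could reverse the bias.
5. Report events found only at the dosing visit, any extra day-3 visit or the calls in a separate descriptive post-dose safety table with no control column.

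The cost is one form field, a short addition to 13.3 and consistent wording of the visit schedule; the analysis change needs no added visits. The small downside is that acute, non-serious events found only at treated-only contacts will have no control comparison.

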## Feasibility assessments

The primary outcome for the trial is feasibility. This will be based the following feasibility targets:

- Recruitment rates to time & target >66% at end of the trial
- Attrition rate of <20% (nb this relates solely to attrition due to loss to follow up or participant withdrawal, it does not include attrition due to participant death)
- Data completeness rates >90%

In addition, data will be collected on specific elements of the TwiC methodology to explore the acceptability of the trial design to participants. This will include determining how many participants in the control arm were aware that the intervention arm existed, and that they had been randomised to be controls. Information will also be collected on the number of participants who were randomly selected to receive either OK432 or BCG, but declined to do so. These participants will continue to be followed up in accordance with the TILT protocol. In order to determine whether participants who decline bacterial immunotherapy differ in any way to other study participants, their baseline characteristics and clinical outcomes will be compared with the control arm and with participants who received immunotherapy, as described in Section 13.

Data from ASSESS-meso will also be used to explore the characteristics and outcomes of patients who consented to join ASSESS-meso but declined to be considered for future trials.

## Efficacy assessments

Exploratory efficacy data will be collected at trial assessment visits. This will include blood tests, including the biomarker mesothelin, tumour response rates based on CT appearances and assessed using the modified RECIST criteria,^42^ and effect on pleural fluid, based on pleural fluid drainage diaries and pleurodesis rates. Patient-reported outcome measures (PROMS) of breathlessness and chest pain, as well as quality of life questionnaires will be completed by the patients at each visit and daily for a period between Week 0 and Week 3. If logistically possible, participants in the BCG arm will undergo Mantoux testing before and after BCG delivery to assess for changes in immunological response. Samples of pleural fluid will be collected at each visit and stored for future testing for cytokine levels and mesothelin. Additional pleural fluid samples will be stored in a pleural fluid biobank for immunophenotyping of T cell populations and further cytokine analysis at a later date. Specific consent to store biological samples for future testing will be obtained at enrolment.

## Safety assessments

Details of adverse event and serious adverse event reporting are presented in section 12. Adverse events will be assessed on each assessment visit and reported on eCRFs and specific adverse event forms. There is a ‘free text’ section on the adverse event form to allow staff to document any specific adverse event features as reported by patients. As well as usual adverse event reporting, eCRFs will specifically record deaths within the study period and episodes of systemic sepsis or pleural infection.

## Source data

Electronic case report forms (eCRFs) will be used to collect data at each study visit. Paper check-lists will be provided to each study centre to use as a prompt for eCRFs if desired. Completed checklists are not classified trial documents and can be filed in the patients’ notes to act as source data or stored or destroyed at the respective study centre.

The primary data source will be the participant’s medical notes. The laboratory reports will form the primary data source for blood results. The CT scan report will form the primary data source for any scans. Assessment of response will be undertaken by an independent, blinded radiologist, and confirmed and the regional MPM MDT.

The screening logs, consent forms and eCRFs will be the source data for the research-specific data. Patient-reported outcome measures, such as symptoms, quality of life and pleural fluid drainage, will use the individual participants’ diaries as source data.

